### Exposure ascertainment

The exposure in this study, for both the primary and secondary aims, will be CCB dispensing including both combination and monotherapy products. Exploring the impact of confounding by indication for non-CCB AHT medicines is important because a modest increased risk of cancer in individuals with hypertension has been documented.^33^ To avoid this issue, previous studies have used a comparator group of patients exposed to other AHTs and/or with a hypertension diagnosis.^34^ Our study population is defined by the presence of hypertension since comparing only to a reference AHT medicine group risks biasing towards the null, if the comparator drug is associated with the outcome. Thus, to reduce bias to the null, women who are both AHT and CCB naïve will be included in the study as long as they meet the entry criteria of hypertension at baseline as described previously. To ensure that exposure to other AHT medicines is accounted for, the cumulative dose-duration exposure of other prescribed AHT medicines (combined) will be captured in the same way as that described for CCB exposure. Thus, in our study, the following four exposure states will be possible during follow-up: (1) women with no exposure to either CCBs or other AHTs; (2) women exposed to other AHTs but not exposed to CCBs; (3) women exposed to CCBs but not exposed to other AHTs and (4) women exposed (at any time) to both CCBs and AHTs. To compensate for immortal-time bias, and to be able to capture the dose–response nature of the association of CCB exposure with risk of breast cancer, a time-varying continuous ascertainment of cumulative exposure (dose duration) to CCB (and separately other AHTs) will be captured as follows.^35^

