For all longitudinal cohorts, the total cumulative duration exposed and the total cumulative dose of each AHT drug class will be calculated from the medicine records available from entry to exit of the study. For all cohorts, the data include information on the date of dispensing, quantity dispensed and the strength of the medicine (derived from the PBS item code for Australian data). In the Rotterdam data, the daily prescribed dose and prescribed duration of use are also available.^29^ This information is not present in the Australian data necessitating estimation of the duration of the medicine. For the Australian data, the reverse waiting time distribution method with multiple random index dates will be used to determine the following: (1) the median duration of medicine possession, defined as the number of days that 50% of prevalent users of the same medicine refill their scripts and (2) the upper duration limit of medicine possession, defined as the number of days that 80% of prevalent users of the same medicine refill their scripts.^37 38^ The median duration will be used as the usual possession duration of the medicine in calculating the total duration (days) of medicine possession in contiguous periods of exposure. The contiguous period will be defined as a series of dispensings of the same AHT class with no break between dispensing that is greater than the upper duration limit of medicine possession of the last medicine in the series. The total cumulative duration (days) of exposure to each AHT class under investigation for each individual over the study period will be the sum of the number of days accrued over all contiguous periods of exposure. The total cumulative dose will be similarly captured across all contiguous periods of exposure by summing the total milligrams (mg) of medicine dispensed of all dispensations (strength/unit multiplied by total units dispensed).

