### Subgroup analysis

In addition to our analysis of overall CCB exposure, the analysis for each aim will be conducted separately according to CCB class (ie, dihydropyridines and non-dihydropyridines) and duration of action (ie, short or long action) where sufficient statistical power exists. Moreover, we will conduct a subgroup analysis to assess the influence of a personal history of any cancer at cohort entry on the risk of breast cancer and CCB exposure.

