### Sensitivity analyses

We will conduct several sensitivity analyses. Since hyperplasia and atypical lesions are not precancerous, we will test the effect of adding ductal carcinoma in situ as a competing risk in sensitivity analyses rather than as an exclusion criterion. We will explore the impact of imposing various time lags, based on clinical consultation, between the start of follow-up on the outcome to account for latency and plausible timing between exposure and outcome development. The potential impact of reduced exposure resulting from imperfect adherence and prescribing at defined daily dose levels (a statistical measure of drug consumption, defined by the WHO) will be investigated in the dose-duration models and through sensitivity analyses.^36^ We will expand the study population to women with prior CCB use at entry (captured as a starting dose-duration value using available look-back data) to examine the impact of CCB use (overall) on the outcome. Finally, because concessional status for subsidised medicines in Australia can change with age or employment status, we will explore varying the definition of continuous PBS concessional status in Australian women to determine the impact this has on the association of CCB exposure with the outcome. The main analysis for the study will be evidence of 100% concessional status between 2003 and 2012 with a single year of no evidence allowed (ie, at least one dispensation per year, and patient recorded as being on concessional status on each dispensation, with 1 year allowed to vary). This will be varied allowing 2 years of no evidence (the more relaxed scenario) and requiring 100% concessional status across all years (as the most stringent requirement). Sensitivity analyses will be applied to the primary aim in the first instance, and those factors found to be influential will be additionally tested in the secondary aim. Due to the potential duplication of participants who were part of the ALSWH and also enrolled in the 45 and Up Study residing in NSW, we will systematically exclude ALSWH participants residint in NSW in a sensitivity analysis. This exclusion is essential for evaluating the potential impact of duplication on the study results.

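### Cumulative dose adds raw milligrams across different medicines in a class, so the dose terms can reflect which molecule was dispensed rather than treatment intensity

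*Protocol article*

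**What the plan says.** All from the protocol article.

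- **Level of accumulation** (Exposure ascertainment): "the total cumulative duration exposed and the total cumulative dose of each AHT drug class will be calculated from the medicine records available". CCBs (ATC C08) form one of five classes.
- **Unit of dose** (same section): "summing the total milligrams (mg) of medicine dispensed of all dispensations (strength/unit multiplied by total units dispensed".
- **Continuity** (same section): an exposure period is "a series of dispensings of the same AHT class with no break between dispensing that is greater than the upper duration limit", so a change of molecule within the class stays in one series.
- **Products covered** (same section): "The exposure in this study, for both the primary and secondary aims, will be CCB dispensing including both combination and monotherapy products".
- **Adjustment covariate** (same section): "the cumulative dose-duration exposure of other prescribed AHT medicines (combined) will be captured in the same way" as for CCBs.
- **Use in the model** (end of Exposure ascertainment; Statistical analysis): total duration, total dose and their interaction enter the model. The generalised propensity score and the threshold search are built on the same dose-duration exposure.
- **Subclass analyses** (Subgroup analysis): repeated "according to CCB class (ie, dihydropyridines and non-dihydropyridines" and by short or long action, where power allows.
- **Defined daily doses** (Sensitivity analyses): reduced exposure from imperfect adherence and from "prescribing at defined daily dose levels (a statistical measure of drug consumption, defined by the WHO" is to be investigated, both in the dose-duration models and in sensitivity analyses.

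**The concern.** A milligram is a common unit only within one substance. If two medicines in a class are used at different daily milligram amounts, women treated equally intensively for equally long receive different values of cumulative dose. Because duration is already in the model, the dose term is meant to carry intensity. On a raw-milligram scale it carries intensity mixed with molecule identity. The interaction, the propensity score for dose and the thresholds inherit the mixture, so a threshold could mark the boundary between two medicines instead of two exposure levels.

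The covariate for other antihypertensives is more exposed, since it adds milligrams across beta-blockers, diuretics, renin–angiotensin agents and others. The estimates are then pooled over cohorts. If the mix of molecules differs between cohorts, coefficients per milligram could differ with no difference in the underlying relationship. Characterising dose-response is part of the primary aim and the first strength that the article lists.

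**Working it through.** The article gives no figure that depends on this definition, and no strengths, market shares or durations. The check is therefore illustrative, and every numerical input below is an assumption.

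**Set-up.** Two molecules. The second has *k* times the usual daily milligrams of the first and is taken by a share *s* of users (10%, 20% or 30%). Relative strength *r* within each molecule is 1 or 2 with equal probability, so E(*r*) = 1.5 and E(*r*²) = 2.5. Duration *D* is independent of molecule and strength, scaled to mean 1, with squared coefficient of variation *c*². Two shapes are used:

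- uniform over 0.5–10 years: *c*² = (9.5²/12)/5.25² = 0.273
- gamma with shape 1.5: *c*² = 1/1.5 = 0.667

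Cumulative milligrams = *r* × *K* × *D*, with *K* = 1 or *k*. Standardised dose = *r* × *D*.

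**Formulas.**

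- E(K) = 1 + s(k−1); E(K²) = 1 + s(k²−1); V = s(1−s)(k−1)²
- Var(mg) = 2.5(1+c²)E(K²) − 2.25E(K)²
- Share of variance in cumulative mg explained by molecule = 2.25V / Var(mg)
- Share explained by molecule (with its product with duration) of what a linear duration term leaves = 2.25V / [2.5E(K²) − 2.25E(K)²]. The duration distribution cancels.
- r² of cumulative mg with standardised dose = E(K)²[2.5(1+c²) − 2.25] / Var(mg)

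**One case in full** (k = 36, for example 5 v 180 mg/day, which over 5 years is 9.1 g v 328.7 g; s = 0.1; uniform durations):

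- E(K) = 4.5, E(K²) = 130.5, V = 110.25
- Var(mg) = 415.3 − 45.6 = 369.7
- Molecule share = 248.1/369.7 = 0.67
- Share after duration = 248.1/(326.25 − 45.56) = 0.88
- r² = 20.25 × 0.932/369.7 = 0.05

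**Ranges over s = 10–30% and both duration shapes.**

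| Ratio k | Molecule share of cumulative mg | Molecule share after duration | r² with standardised dose |
|---|---|---|---|
| 1 (after conversion) | 0% | 0% | 1.00 |
| 2 | 7.5–21% | 38–50% | 0.70–0.86 |
| 4 | 28–46% | 74–76% | 0.34–0.49 |
| 10 | 39–62% | 83–86% | 0.13–0.27 |
| 36 | 44–67% | 86–88% | 0.05–0.19 |

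A simulation of 400,000 women at k = 2 and k = 36 agreed with the first and third result columns to within 0.01. A more skewed duration distribution (gamma, shape 1.2) lowers the first column to 6–10% at 2-fold, 24–26% at 4-fold and 35–45% at 10- to 36-fold. The second column does not change.

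**The case against.** Much of the plan does not depend on milligrams. Duration is counted in days and enters separately, so a duration-response can be estimated, and the aim is framed around long-term use. The matched comparison of exposed with non-exposed women is also untouched. A reader might infer that the dose-response aim cannot be answered at all; the article does not support that. This objection stands and limits the point to the dose terms.

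Defined daily doses are not absent. A reader might infer that they are confined to an adherence sensitivity analysis, but the Sensitivity analyses section places them in the dose-duration models as well. It does not say that milligrams will be divided by the defined daily dose, and the primary definition is unchanged, so this is a partial answer at best.

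The subclass analyses help to the extent that the milligram gap lies between dihydropyridines and non-dihydropyridines. They depend on power, can still sum several molecules within a subclass, and leave the other-antihypertensive covariate as it is.

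Two further points are inference. The Introduction describes country differences in the use of CCBs as a class, not in which molecules are used, so different mixes could appear as differences in dose-response; it cannot be said that they would. For combination products the article is silent on whether partner-drug milligrams count. The caption of Figure 2 speaks of each medicine instead of each class, but the figure is not shown and the text says class.

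**Conclusion.** The point holds for the cumulative-dose term, its interaction with duration, the generalised propensity score for dose, dose thresholds and the covariate for other antihypertensives. As written, the rule allows molecule choice to pass as dose. That the rule is stated without a common scale is certain from the text; the size of the effect is not.

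A reader might infer that cumulative dose mainly identifies the molecule. That holds only under some assumptions. Conditional on duration, molecule accounts for up to half of the remaining variation at a 2-fold ratio and about three quarters or more from 4-fold upwards. For crude cumulative milligrams it stays below half at 4-fold, and at 10- to 36-fold it passes half only for some duration distributions. At a 2-fold ratio, raw milligrams still track standardised dose fairly well (r² 0.70–0.86). All of this rests on the two-molecule set-up, the 10–30% shares, the 2-fold strength range and duration being independent of molecule.

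**What to change.** - In the primary models, the generalised propensity score and the threshold search, define cumulative dose as the sum over dispensings of mg dispensed divided by the WHO defined daily dose of that ATC level-5 substance. Do this for CCBs and for other antihypertensives.
- State that only the CCB component of a combination product counts towards CCB dose.
- Keep raw milligrams only for analyses within a single substance.
- Reword the defined-daily-dose sentence in Sensitivity analyses so that it is clear what is converted, and in which models.

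The inputs are at hand: level-5 codes are listed in a supplement, strength and quantity are available in all cohorts, and the article cites the same reference for the ATC codes and for defined daily doses. The cost is one lookup table and a few sentences of text. The drawback is that defined daily doses are conventional units, not exact potency equivalents, so some molecule effect may remain. This concerns the measurement scale only and is not a recommendation on dosing.

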**Figure 2 F2:**
[figure not shown]
Capture cumulative dose and duration exposed for each antihypertensive medicine.

In addition, time since last CCB exposure will be calculated in months from exit of the cohort back to the date of the last CCB exposure to differentiate between recent and previous exposure. This value will range from 0 for those with current exposure at the time of exit to the total of the follow-up time for those who are never exposed.

In the statistical model, dose duration will be captured by three elements, total cumulative duration, total cumulative dose and an interaction term to evaluate effect modification between duration and dose.

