**Methods and analysis:**

The study will use data from 2 of Australia’s largest cohort studies; the Australian Longitudinal Study on Women’s Health, and the 45 and Up Study, combined with the Rotterdam Study. Eligible women will be those with diagnosed hypertension, no history of breast cancer and no prior CCB use at start of follow-up (2004–2009). Cumulative dose-duration exposure to CCB and other AHT medicines will be captured at the earliest date of: the outcome (a diagnosis of invasive breast cancer); a competing risk event (eg, bilateral mastectomy without a diagnosis of breast cancer, death prior to any diagnosis of breast cancer) or end of follow-up (censoring event). Fine and Gray competing risks regression will be used to assess the association between CCB use and development of breast cancer using a generalised propensity score to adjust for baseline covariates. Time-varying covariates related to interaction with health services will also be included in the model. Data will be harmonised across cohorts to achieve identical protocols and a two-step random effects individual patient-level meta-analysis will be used.

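### CCB exposure is promised as time-varying but defined as totals at study exit; if those values enter as fixed covariates, the CCB effect is biased strongly downwards

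*Protocol article*

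**What the plan says.** All places are in the protocol article.

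- **Exposure ascertainment, opening paragraph.** To deal with immortal-time bias and to capture dose–response, the authors announce "a time-varying continuous ascertainment of cumulative exposure (dose duration) to CCB", and say that the details follow.
- **Exposure ascertainment, the details.** Total duration and total dose of each drug class "will be calculated from the medicine records available from entry to exit of the study".
- **Exposure ascertainment, text after Figure 2.** For recency, "time since last CCB exposure will be calculated in months from exit of the cohort back to the date of the last CCB exposure". The value runs from 0 for current users "to the total of the follow-up time for those who are never exposed". The model terms are then listed: "dose duration will be captured by three elements, total cumulative duration, total cumulative dose and an interaction term". Recency is not in that list.
- **Abstract, Methods and analysis.** "Cumulative dose-duration exposure to CCB and other AHT medicines will be captured at the earliest date of: the outcome", a competing event or the end of follow-up.
- **Statistical analysis.** The primary model is Fine and Gray regression, with a generalised propensity score for continuous exposure. A time-dependent dose–response component is described as a further extension. Exposed and non-exposed women are also to be compared by binary propensity score matching.
- **Study population.** Women with CCB use before entry are excluded, so all CCB exposure in the main analysis arises after entry.

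**The concern.** The announced remedy and the definitions that are meant to deliver it disagree. A time-varying exposure has a value at every follow-up time, built from what happened before that time. The article defines one value per woman, read off at her exit date. That date is the outcome time for cases and the censoring or competing-event time for everyone else. Longer event-free follow-up leaves more time to start and accumulate CCB use, so an exit total partly measures survival.

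The recency coding has the same fault more plainly: for a never-exposed woman the value is her follow-up time.

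The dose–response estimate is the primary aim. The Discussion says that a finding of no association would reassure women about current guidelines, so a bias that hides harm is the error that matters most here.

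**Working it through.** **1. The plan's own figures.** The article gives no figure for this bias. Its only effect-size figure is a minimum detectable effect of ±0.2 (Sample size calculation). That cannot be reproduced, because the numbers exposed are in a figure that is not shown and the text gives neither event rate nor scale. The point does not depend on it.

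**2. Why the direction is downwards.** When a case is diagnosed at time t, her exit total is her exposure up to t. A woman still under follow-up at t carries her total up to a later exit, which can only be equal or larger. Cases therefore look less exposed than the women they are compared with, even if CCBs do nothing.

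An illustration with an assumed CCB start rate of 4% per year:
- P(ever-user by year T) = 1 − exp(−0.04 × T), so the odds are exp(0.04 × T) − 1.
- Case at year 5: probability 0.181, odds 0.221.
- Comparison woman followed to year 9: probability 0.302, odds 0.433. Ratio 0.221/0.433 = 0.51.
- Comparison woman followed to year 13: probability 0.405, odds 0.682. Ratio 0.221/0.682 = 0.32.

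This shows the mechanism in one risk set and ignores deaths. The simulations below average over follow-up.

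**3. Simulations.** All rates are assumptions; none comes from the article.
- *A:* 800,000 women; breast cancer 0.35%/yr; death 2–8%/yr; CCB start 3%/yr; censoring at 9–12 years; partial likelihood on sampled risk sets (4,000 cases, 60 controls).
- *B:* 12,000 women; breast cancer 0.35%/yr; death 2% or 5%/yr; CCB start 4% or 8%/yr; CCB stop 5% or 15%/yr; censoring at 9–13 years; 6 or 8 replicates per setting. The exit-value fits are Fine and Gray. Time-updated exposure changes every half-year.

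| Hazard ratio | Exit value as fixed covariate | Time-updated, cause-specific | Time-updated, Fine and Gray, exposure frozen at death |
|---|---|---|---|
| No true effect: per year of use | A 0.81–0.83; B 0.82–0.84 | A 0.99–1.01; B 0.99–1.01 | B 1.04–1.08 |
| No true effect: ever-use | B 0.47–0.55 | B 1.00–1.01 | B 1.10–1.23 |
| No true effect: duration + dose + interaction, 5 years v none | B 0.36–0.43 | not run | not run |
| True ever-use ratio 1.2: ever-use | B 0.57–0.66 | B 1.22 | B 1.33–1.48 |

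The first column is biased downwards in every setting tried. Duration and dose alone are enough to produce this; recency is not needed.

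**4. Recency as coded.** Used alone as an exit value, with no true effect, recency gives 0.87–0.91 per year in B. Added to duration, it lowers the duration ratio further: to 0.28–0.37 per year in A and 0.56–0.72 in B. The direction agrees, but the size does not, so no single figure should be quoted for it.

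**5. Why time-updating inside Fine and Gray is not enough.** That model keeps women who died in the risk set. If their exposure is held at its value at death, they look less exposed than living women, and the null estimate rises. The ever-use log hazard ratios were 0.094 (SE 0.039) at 2%/yr mortality and 0.203 (SE 0.062) at 5%/yr.

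**The case against.** The strongest reply is that the authors name immortal-time bias themselves, declare a time-varying exposure against it, and add a time-dependent component in the Statistical analysis section. Dispensing dates are held for all cohorts, so an entry-to-exit total could be just the last value of a time-updated series. Data layout is commonly left to an analysis plan, and the figures that depict exposure capture are not shown.

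Much of this stands. No sentence says that exit totals enter as fixed covariates, so the bias is conditional. But the exit-anchored definitions are stated rules, not missing detail, and they are what the time-varying promise points to. The Covariates section says that statin and hormone use are updated annually; no such rule is given for CCB exposure. The time-dependent component is something the authors will do in addition. The matched comparison of exposed with non-exposed women has no time-updated definition at all.

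Three stronger readings are tempting and not supported:
- *That recency is certainly a regressor.* It is defined to separate recent from past exposure, but it is not among the listed model elements and its role is not stated.
- *That the bias is downwards whatever is done.* Time-updated exposure in Fine and Gray, frozen after death, moved the estimate upwards.
- *That most women are planned to be never-exposed.* The 5:1 ratio is an assumption of the power calculation, not a planned composition.

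It is also fair that neither simulation includes the generalised propensity score or the threshold model.

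**Conclusion.** The point holds as a contradiction with a serious conditional consequence. The definitions in the Abstract and in Exposure ascertainment do not deliver the time-varying exposure announced in the latter section, and the value given to never-exposed women is the survival time itself.

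If exit values or ever/never status are used as fixed covariates, the distortion exceeds the effect the study hopes to detect, provided that the ±0.2 is a relative effect. For ever-use under the null it is at least 1 − 0.55 = 0.45 on the ratio scale, and a moderate true harm would appear as protection. The sizes rest on assumed rates; the direction held in all the exit-value settings tried.

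A reader might infer that the primary result is bound to be an artefact. The documents do not support that, because they also state time-varying intent. They do leave open an analysis that could reverse the sign of the primary answer, so the text should be corrected before analysis.

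**What to change.** 1. Define cumulative duration, cumulative dose and, if modelled, recency at each follow-up time t from dispensings before t only. Apply this to the main model and to the exposed v non-exposed comparison.
2. Delete the rule that gives never-exposed women their follow-up time. Make never-exposed a separate category, and code recency only among women already exposed by t. State whether recency enters the model.
3. Bring the Abstract and the later paragraphs of Exposure ascertainment into line with that section's opening promise.
4. Estimate the time-varying effect in a cause-specific hazard model and say that this is the estimand, or keep Fine and Gray and state how exposure is handled after death or bilateral mastectomy.

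The cost is a start–stop data layout, revised wording and some extra analysis. No new data are needed.
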